## Abstract

**Background:**

Adolescent girls and young women constitute a priority population disproportionately affected by HIV, accounting for 25% of annual HIV incidence among people older than 15 years in Kenya. Although oral preexposure prophylaxis (PrEP) is effective in reducing HIV acquisition, its protective benefit has been limited among adolescent girls and young women in sub-Saharan Africa because of low uptake, adherence, and persistence. Intimate partner violence (IPV) and relationship power inequities are widespread among adolescent girls and young women and contribute to higher HIV incidence and lower PrEP use. Interventions are needed to support sustained PrEP use among adolescent girls and young women by addressing IPV and relationship dynamics.

**Objective:**

This study aims to test the effectiveness of Tu’Washindi na PrEP (“We are Winners with PrEP”), a multilevel community-based intervention, to increase uptake and adherence to PrEP and reduce IPV among adolescent girls and young women in Siaya County, Kenya.

**Methods:**

The Tu’Washindi na PrEP intervention was co-designed by our team and adolescent girls and young women using participatory methods and includes 3 components delivered over 6 months: an 8-session, empowerment-based support club for adolescent girls and young women, community sensitization targeted toward male partners, and PrEP education events for couples. The intervention will be evaluated using a cluster randomized controlled trial across 22 administrative wards in Siaya County, Kenya, enrolling 72 adolescent girls and young women per ward (total N=1584). The primary objectives are to test the effectiveness of the intervention on PrEP uptake and adherence immediately after delivery (month 6 after enrollment) and 6 months later (month 12). As secondary objectives, we will test the intervention effect on IPV. A rigorous process evaluation will explore mechanisms of change, contextual factors, and implementation considerations to inform future refinement and scale-up, using programmatic data, participant questionnaires, and qualitative interviews with participants and intervention providers.

**Results:**

Data collection started in September 2022. As of December 2024, enrollment has been completed in 16 of the 22 study wards, with 72.6% (1150/1584) of participants enrolled. We anticipate that data collection will be completed in May 2026 and results will be available by mid-2027.

**Conclusions:**

The study builds directly on our promising formative and pilot research to develop the evidence base for this youth-designed, multilevel HIV prevention intervention. If effective, Tu’Washindi will be ideally positioned for sustainable integration into existing youth-focused programming to expand and support PrEP use in this priority population.

**Trial Registration:**

ClinicalTrials.gov NCT05599581; https://www.clinicaltrials.gov/study/NCT05599581

**International Registered Report Identifier (IRRID):**

DERR1-10.2196/55931

## Introduction

### Background

Optimizing the effectiveness of proven biomedical prevention interventions is critical to decreasing the high incidence of HIV among adolescent girls and young women aged 15 to 24 in sub-Saharan Africa, a priority population for HIV prevention. More than 1 in 4 new HIV infections in this region are among adolescent girls and young women [1], who are over twice as likely to acquire HIV as their male counterparts [2]. Oral preexposure prophylaxis (PrEP) is an effective, female-initiated biomedical HIV prevention intervention, but its protective benefit has been limited among adolescent girls and young women across sub-Saharan Africa by challenges to uptake, adherence, and persistence [3-17]. In western Kenya, a study of adolescent girls and young women attending family planning clinics found that 76% met PrEP eligibility criteria, but only 4% initiated PrEP [16], and the proportion of adolescent girls and young women persisting with PrEP for 3 months postinitiation ranged from 5% to 37% across studies [7,10,11,15,17]. In samples of PrEP users at an average of 6 months postinitiation, only 4% to 8% had tenofovir diphosphate (TFVdp) levels suggesting high adherence [4-6]. The public health impact of PrEP will be determined by concurrent interventions that address critical barriers to uptake and adherence.

Adolescent girls and young women who live in a context of heightened gender inequality and risk of intimate partner violence (IPV) represent a large subpopulation who are uniquely vulnerable to HIV infection. IPV is widespread among adolescent girls and young women in western Kenya: 19% reported experience of sexual IPV in the past year, 25% reported physical IPV, and 34% reported emotional IPV [18-20]. Experience or fear of IPV in sexual relationships is associated with having limited relationship power [20,21] and with 28% to 55% higher HIV incidence in adolescent girls, young women, and adult women [21-23]. Studies have found that IPV and other partner-related social harms are associated with 1.5- to 2.5-fold higher risk of poor adherence to oral PrEP and the dapivirine ring for HIV prevention. Similar to HIV treatment and contraception [19,20,24-29], IPV and relationship inequality introduce barriers to uptake of and adherence to PrEP at multiple levels. At the individual-level, restricted access to information and health services, poor negotiation skills, low self-efficacy, and fear of violence or relationship dissolution hinder adoption of health-promoting behaviors [30-32]. Dynamics at the partner level, such as poor communication and low decision-making power, limit disclosure about PrEP use and reduce partner support, which can impact adherence [33-35]. These challenges are further compounded at the community level by a lack of PrEP awareness, inequitable gender norms, and stigma associated with taking PrEP, which contribute to partner and community opposition to female PrEP use [36-39]. A multilevel context-specific intervention to address barriers to PrEP use is needed to ensure that adolescent girls and young women experiencing relationship inequality and IPV benefit from this effective biomedical prevention strategy.

In response, our intervention, Tu’Washindi na PrEP (We are winners with PrEP), was designed in close partnership with local adolescent girls and young women and incorporates strategies targeted to address relationship dynamics and IPV at multiple levels [40,41]. This intervention has 3 components: an empowerment-based support club for adolescent girls and young women, PrEP education events for couples offered in the context of a health fair (Buddy Days), and community sensitization about PrEP targeted toward adolescent girls and young women’s partners [40]. The pilot cluster randomized controlled trial (cRCT) of Tu’Washindi at 6 Determined, Resilient, Empowered, AIDS-free, Mentored and Safe (DREAMS) spaces demonstrated feasibility, high acceptability, implementation with fidelity, and promising effects on PrEP and IPV outcomes [42]. PrEP uptake and adherence were both approximately twice as high in the intervention arm as in the control arm (*P*<.05) [43]. Although the adherence was still lower than desired in the intervention arm, with Wisepill openings on 25% of days on PrEP, they still represented substantial improvement over programmatic outcomes [6,17]. We also observed less frequent or severe IPV among intervention arm participants [43].

Because our pilot findings suggested that Tu’Washindi shows promise as an acceptable intervention that can be implemented with fidelity to promote PrEP uptake and adherence among adolescent girls and young women without concomitant increases in IPV, we designed a fully powered effectiveness trial to determine whether these gains translate to increases in biomarker measures of PrEP adherence and whether the intervention can reduce IPV risk.

### Study Objectives

The objective of this study is to test the effectiveness of the multilevel Tu’Washindi intervention to increase effective PrEP use and reduce IPV among Kenyan adolescent girls and young women by addressing relationship dynamics and partner opposition to PrEP. A process evaluation will assess the implementation processes and theorized mechanisms of change influencing intervention effectiveness and identify implementation challenges and strategies to facilitate future scale-up in programmatic settings to maximize public health impact. Study findings will contribute to the limited evidence base for effective PrEP adherence interventions to reduce HIV acquisition in this priority population.

## Methods

### Design

This study has a 2-arm parallel cRCT design (Figure 1). We have randomized 22 administrative wards in a 1:1 ratio and aim to enroll about 72 adolescent girls and young women from each (total N=about 1584) to receive either the Tu’Washindi intervention plus usual HIV prevention services, or usual HIV prevention services alone. Because of the urgent need for interventions to support PrEP use among adolescent girls and young women in a real-world context, the intervention is delivered outside of DREAMS to evaluate its impact on adolescent girls and young women accessing PrEP from Ministry of Health (MoH) facilities. This pragmatic study design enables us to determine effectiveness of the intervention when layered onto ongoing county-wide HIV prevention programming [44]. After informed consent and baseline data collection, the Tu’Washindi intervention is implemented in each intervention cluster while the control cluster continues with usual HIV prevention services. The duration of study participation is 12 months, with data collection visits at intervention midline (study month 3), intervention endline (study month 6), and at 6 months postintervention (study month 12). A prospective process evaluation is being conducted to characterize intervention implementation, explore theorized mechanisms of change, and capture contextual factors influencing study outcomes. The protocol was written following the 2013 SPIRIT (Standard Protocol Items: Recommendations for Interventional Trials) guidelines (Multimedia Appendix 1).

**Figure 1 figure1:**
[figure not shown]
An overview of the study design. AGYW: adolescent girls and young women; FTCtp: emtricitabine triphosphate; IDI: in-depth interview; IPV: intimate partner violence; PrEP: preexposure prophylaxis; TFVdp: tenofovir diphosphate.

### Study Setting

Siaya County is located in the former Nyanza Province in western Kenya, along the shores of Lake Victoria. The county is primarily periurban and rural, and agriculture and fishing are the main economic activities [45]. Siaya County has the second highest HIV incidence in Kenya (2.5% per year); it is the site of 12% of new HIV infections but comprises just 2% of the national population [46]. In addition, the former Nyanza Province has the highest prevalence of gender-based violence in Kenya: 22% of women aged 15 to 49 have reported sexual violence and 56% have reported physical violence at least once since the age of 15 [18].

### Study Organization

The Tu’Washindi study leadership is comprised of investigators from RTI International and Impact Research and Development Organization (IRDO) and meets monthly. This group is ultimately responsible for the design and conduct of the trial, including intervention updates, protocol preparations and revisions, and protocol and safety monitoring. The trial management committee meets weekly, and it is responsible for the day-to-day conduct of the trial. It includes the principal investigator (PI) and site PI, project director and project coordinator, intervention leads, and quantitative and qualitative data management teams. The University of North Carolina Center for AIDS Research Clinical Pharmacology and Analytical Chemistry Core is responsible for analysis of the dried blood spot (DBS) samples. The study is further supported by a 5-member national-level technical advisory committee who meet annually and advise on design considerations to ensure a smooth transition from research to implementation if the intervention is effective; a 15-member youth advisory board that meets quarterly and provides feedback on study design and methods, data collection tools, and recruitment and retention of study participants; and a 12-member stakeholder advisory board made up of PrEP technical staff from MoH and other delivery partners, IPV referral agency representatives, and other community leaders that meets twice yearly to advise on effective integration of the study into existing structures and on linkage to PrEP and other referral services.

### cRCT Component

#### Site Selection and Randomization

The study clusters comprise 22 of the 30 administrative wards in the county. The 30 wards were categorized into 5 strata based on community type (ie, periurban, rural fishing, or rural nonfishing) and whether the proportion of girls on PrEP is above or below the median, using MoH programmatic data. (Although the geography and PrEP use criteria define 6 strata, only 1 ward in the county fell within the urban, low PrEP use stratum. Because it was not possible to create a pair of intervention and control wards in this stratum, it was excluded.) The 22 study wards were purposively selected to ensure an even number of wards within each stratum and a balanced distribution of wards across strata. Randomization was completed by RTI statisticians once the 22 study wards are selected and placed into strata. Within each stratum, wards were randomly allocated to the intervention or control arms in a 1:1 ratio. After randomization, we created pairs of intervention and control wards within each stratum and determined the order in which they would be enrolled in the study based on the location of each ward, to minimize the risk of contamination while ensuring the feasibility of implementation. Subsequently, one intervention and control site pair were randomly selected from each stratum for inclusion in the qualitative component. Allocation was revealed to the investigators before community mapping (see the Recruitment and Screening section) and to the participants after their enrollment into the study.

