#### Eligibility Criteria

To be eligible, potential participants must be females aged 15 to 24, currently in a sexual relationship with a male partner for at least 1 month, and vulnerable to HIV per a modified version of the DREAMS eligibility screening tool. To reflect the population most likely to participate in this intervention in a programmatic setting, they must be either taking PrEP or interested in taking PrEP (ie, she thinks that she would benefit from PrEP but is not currently taking it). In addition, they must be residents of the applicable study ward; willing and able to attend support clubs; willing and able to provide adequate contact information; fluent in English, Dholuo, or Kiswahili; and able and willing to provide informed consent (or assent and parental consent for nonmature minor participants aged 15 to 17). Potential participants are excluded if they are living with HIV (by self-report); planning any long-term travel or relocation in the next 12 months; or have any condition that the site PI or designee determines would preclude participation.

Individuals who do not meet the criteria for participation in this trial (ie, screen failure) because of criteria that are likely to change over time may be rescreened. Examples include not being resident of the ward or not being interested in taking PrEP.

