#### Recruitment and Screening

Recruitment occurs simultaneously in each pair of wards before moving on to the next pair and focuses on the catchment areas of 2 to 4 health facilities in each ward. Before recruitment, community mapping is conducted to identify key stakeholders, referral resources, locations where adolescent girls and young women gather, and locations where men gather. Recruitment takes place at venues identified through community mapping, including health facilities, schools, churches, DREAMS Safe Spaces, youth groups, and community markets. To ensure that the study findings are generalizable to adolescent girls and young women across the 15- to 24-year age range, we aim to enroll at least 25% of the study participants from the 15- to 19-year age group who have lower rates of PrEP use but have similar HIV incidence to the 20- to 24-year age group [47,48]. Attendees interested in the study are invited to meet with the research assistant after the recruitment meeting to discuss questions, obtain additional information, and schedule an appointment for informed consent, eligibility screening, and, if eligible, for enrollment.

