##### Intervention Delivery

Before delivery, the intervention manual and training tools were updated to reflect lessons learned during the pilot and the change to implementation outside of DREAMS. Because age restrictions on PrEP in DREAMS did not permit us to pilot the intervention with adolescent girls aged 15 to 17 years, we pretested the activities with 12 to 15 adolescent girls in this age range over a 1-month period to obtain feedback on comprehension and relevance of the content and how best to support participation.

Delivery takes place in 4 phases, with activities occurring concurrently in 2 wards during phase 1 and in 3 wards during phases 2 to 4. In each ward, the intervention is conducted over a 6-month period with intervention implementation beginning about 1 week after enrollment concludes. Each new phase of the intervention commences immediately after the activities in the previous phase are concluded. This phased approach minimizes staff burden and allows for close monitoring of implementation to identify and correct problems early on.

The intervention activities include sensitization of MoH clinics, intervention staffing and training, community sensitization sessions, Buddy Days, support clubs, and monitoring and quality assurance.

For sensitization of MoH clinics, before study initiation in each intervention ward, we collaborate with the facility in-charges from each of the 2 to 4 health facilities selected for study recruitment to identify PrEP delivery staff and schedule a half to one day training to introduce the study and discuss relationship-related challenges to PrEP use, with the goal of ensuring that the counseling support offered at the clinics complements the messages provided through the intervention. We also review PrEP adherence and couples’ counseling and disclosure approaches to more comprehensively address adherence challenges commonly experienced by adolescent girls and young women.

Intervention staffing and training within each ward is delivered by a set of 2 to 4 mentors (ie, women slightly older than the participants who have completed at least some secondary education and are rooted in their communities), an experienced male community organizer, and clinicians and counselors with experience in PrEP provision to adolescent girls and young women (hereafter “intervention providers”). Staff supervisors train each cadre over 1 to 3 days to review the intervention manual and to practice the required activities.

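### The plan ties disclosure of the ward's arm to participants' enrollment, not to the close of ward enrollment, so later recruits may know the arm before they consent

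*Protocol article*

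**What the plan says.** All references are to the protocol article.

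- **Unit of allocation** (Site Selection and Randomization): "Within each stratum, wards were randomly allocated to the intervention or control arms in a 1:1 ratio". One woman's arm is therefore the arm of everyone in her ward.
- **Who learns it, and when** (same section): "Allocation was revealed to the investigators before community mapping", "and to the participants after their enrollment into the study". The sentence does not mention the end of ward recruitment.
- **How women enter** (Recruitment and Screening): after a recruitment meeting, interested attendees talk to a research assistant and "schedule an appointment for informed consent, eligibility screening, and, if eligible, for enrollment". The venues are shared ones such as schools, churches, youth groups and markets.
- **What they must declare** (Eligibility Criteria): among other things, being "willing and able to attend support clubs", and either current PrEP use or interest in it. Women who fail screening for lack of interest in PrEP may be rescreened.
- **When delivery begins** (Intervention Delivery): in each ward over a 6-month period, "with intervention implementation beginning about 1 week after enrollment concludes".

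**The concern.** In a cluster trial that recruits individuals after randomization, the balance gained by randomizing wards protects the comparison only if knowledge of the arm does not influence who joins. Once one woman has been told, others in her ward can learn whether joining brings support clubs and couples' events or usual services only. Willingness to attend clubs is then a real commitment in an intervention ward and an empty one in a control ward. Rescreening adds a route: a woman first screened out for lack of interest in PrEP has a reason to come back in a ward known to be intervention that she lacks in one known to be control.

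The primary outcome is effective PrEP use among all participants, and both current users and merely interested women may enter. A shift in that mix that differs by arm would move the outcome directly. Motivation and openness to partner involvement could also affect the IPV outcomes.

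**Working it through.** The plan gives no figure on this point, so there is none to reproduce. The check is of wording and sequence, followed by an illustration.

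**1. Individual or ward-level disclosure?** The wording allows both. Where the article means closure of a ward it says so in other terms: Intervention Delivery speaks of enrollment concluding, and Results of enrollment being completed in wards. Where it means one woman, it uses enrollment as an individual event: Retention refers to a participant once enrolled, and Table 3 lists enrollment as a month 0 procedure. The disclosure sentence resembles the second usage. Individual disclosure is the more natural reading, but it is not proven.

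**2. Does individual disclosure expose later recruits?** Appointments are booked individually, so entry within a ward appears staggered. With 72 women per ward, at most 72 − 1 = 71 could enter after the first disclosure. The actual share cannot be derived.

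**3. Could the analysis repair it?** Only in part. Dried blood spots are taken at months 6 and 12 only (Table 4), so there is no baseline biomarker; PrEP history at baseline comes from a questionnaire. Analysis Approach puts control for baseline imbalance into exploratory analyses. Limitations relies on stratifying by two community characteristics, which does not govern who volunteers within a ward.

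**4. Illustration of size.** Let f be the share of a ward recruited with the arm known, and d the resulting difference between arms in effective use among those women. Both are assumptions. Then bias = f × d.

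- f = 25%, d = 5 points: 0.25 × 5 = 1.25 points
- f = 50%, d = 10 points: 0.50 × 10 = 5 points
- f = 75%, d = 20 points: 0.75 × 20 = 15 points

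The design target is 15 points (Sample Size Considerations).

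**5. Effect on type I error.** I used a ward-level t-test with 11 wards per arm, 60 analyzed per ward, 20 df and alpha 0.025. The article does not state sidedness, so two-sided is an assumption. With control proportion p and ward SD s,

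SE = √{2 × [p(1 − p)/60 + s²]/11}.

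For p = 0.10 and s = 0.10: SE = √{2 × [0.0015 + 0.0100]/11} = 0.046. The rejection probability with no true effect comes from the noncentral t distribution with noncentrality bias/SE:

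| Bias | s = 10%, p = 10% / 25% | s = 5%, p = 10% / 25% |
|---|---|---|
| 1.25 points | 0.030 / 0.029 | 0.039 / 0.035 |
| 5 points | 0.113 / 0.101 | 0.308 / 0.219 |

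A mild shift barely matters and a moderate one matters a good deal. The document does not say which applies. If d is negative, the same bias dilutes a true effect.

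**The case against.** The strongest reply is that the plural wording also fits telling all of a ward's women once the ward is full, and that the gap of about a week before delivery leaves room for exactly that. The article condenses a full protocol that is not shown, and that document may settle the timing. It also contains some protection: participants learn the arm after enrollment, consent and baseline data come before delivery, and the entry criteria are the same in both arms.

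This stands as far as it goes. A reader might infer that the plan openly discloses the arm while the ward is still recruiting, or that masking of participants at entry has been lost. The documents support neither: individual disclosure is not stated outright, and the article nowhere claims that participants are masked. A reader might also infer a bias of known size in favor of the intervention. That too is unsupported. Women who join a ward known to be control, with no clubs on offer, could be the more PrEP-motivated ones, which would bias toward no effect.

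What the reply does not remove is that the article states a rule and is not merely silent. Under its more natural reading, the rule permits arm-dependent entry. If ward closure was meant, the sentence needs the same one-line correction.

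It is also fair to say that the timing of disclosure to participants is not the only route. Investigators know the arm before community mapping, and staff at the recruiting facilities in intervention wards are trained before study initiation there. Those routes stay open whatever participants are told.

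**Conclusion.** The concern holds in conditional form. The disclosure rule is not tied to the close of ward enrollment. Read as individual disclosure, it lets later recruits know the arm before consent, so the self-declared entry criteria may select differently by arm, and little in the planned analysis would correct that afterwards. The conclusion rests on that reading, on staggered entry within wards, and on word spreading at shared venues; the second and third are plausible from the recruitment description but not stated.

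Neither size nor direction can be derived from the document. The 1.25 to 15 points shown above reflect assumed inputs and are not estimates. The correction is worth making because it is cheap, not because harm has been shown.

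**What to change.** **Wording.** Amend Site Selection and Randomization to say: *A ward's participants are told the allocation only after that ward's last participant has been enrolled and before delivery starts.* The rule should work ward by ward. Waiting for both wards of a pair could hold up delivery in an intervention ward that fills first.

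**Wards still to be enrolled.** Apply the rule there: 22 − 16 = 6 wards as of December 2024. Data collection is expected to end in May 2026 and follow-up lasts 12 months, so on that timeline the last enrollment falls by about May 2025. If all wards have closed, only the next step remains.

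**Completed wards.** State when participants in each ward were told. Use recorded enrollment dates to compare baseline PrEP use, IPV and age by enrollment order and arm. The contrast of interest is whether the early-to-late change differs between arms, since early and late recruits may differ for other reasons. Report the primary effect in early enrollees as a sensitivity analysis, with the cut-off fixed before outcome data are seen.

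**Cost.** No extra visits. Women wait until ward enrollment closes to learn their arm, and procedures may differ between completed and later wards. The sensitivity analysis loses some precision. For example, with 30 instead of 60 analyzed per ward, p = 0.25 and s = 0.10, the SE rises from √{2 × [0.003125 + 0.01]/11} = 4.9 points to √{2 × [0.00625 + 0.01]/11} = 5.4 points. The change does not remove selection arising from investigators' prior knowledge of the arm or from clinic training in intervention wards.
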